### Sample Size

To establish an appropriate sample size, a power analysis was conducted using G*Power (Erdfelder, Faul, and Buchner) [22,23]. The experimental design has 4 total health centers. Individuals at every health center will be randomly assigned to an intervention arm, keeping in mind that the intervention arm needs to be in multiples of 8 at a time and that intervention groups are equal in size. Baseline characteristics are not expected to affect the outcome. In G*Power, the power analysis was run with 2 groups (the control arm and the intervention arm), which were then split up into 8-equal sized subgroups (health center A intervention, health center A control, ...., health center D intervention, health center D control). The model included 3 time points for measurements. The correlation among repeated measures that varied for a range of values from 0.05 (representing nearly uncorrelated measurements) to 0.3 (representing moderately correlated measurements) was considered. The desired power was always set to 0.8, and the nominal type I error was set to .05. A range of Cohen (1988) effect sizes was evaluated, from 0.10 (very small) up to 0.25 (a medium effect size). The outcome, the mean knowledge of postbirth warning signs, is a continuous variable. This was accomplished by varying the intervention arm’s mean knowledge level. Based on previous study data, 1.9 was used as the control sample’s mean knowledge score, and 1.4 was used as the SD within groups. For the intervention sample, a range of values for the mean knowledge score was tested, from 2.2 (which equates to a 0.1 effect size) to 2.65 (equating to a 0.25 effect size). The control arm and the intervention arm were assumed to have the same SD.

Under optimal conditions, where the correlation among repeated measures is minimal at 0.05 with a medium effect size of 0.25, a total sample size of 64 (16 individuals split into 1 intervention and 1 control group per clinic) is required [24]. Whereas under the worst assumed conditions (a small effect size of 0.10 and any correlation among repeated measures), a total sample size of 512 (128 individuals per clinic split into 16 intervention and 16 control groups) would be necessary. Assuming we want to detect a Cohen f of 0.15 with any size correlation up to 0.3 among repeated measures and no attrition, the recommended sample size is 192 (with 48 individuals split up into 3 intervention and 3 control groups per clinic).

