### Analysis Plan

Differences in outcomes between the intervention and control arms will be assessed. We expect that the intervention arm will have higher knowledge of postbirth warning signs than the control arm at every time point measured and that the intervention arm will have a larger increase in knowledge of postbirth warning signs between time points. We expect postpartum health behaviors to be different between the intervention and control arms.

All data will be reviewed for completeness and transferred to STATA (StataCorp) statistical software for analyses [37]. The primary variable of interest is knowledge of postbirth warning signs, measured on 4 occasions. The baseline measurement of knowledge of postbirth warning signs will be used in an initial *t* test to confirm that there is no difference in knowledge between the intervention and control arms before the study to validate the randomization procedure. We will model and test the difference between intervention and control arm knowledge of postbirth warning signs at each time point, and knowledge between time points will be assessed using a repeated measures multivariate ANOVA (MANOVA) with a time and treatment interaction as the primary analysis controlling for baseline demographic variables. For the intervention arm, follow-up secondary analyses will measure the change in postpartum health status, postpartum health behaviors, and clinical assessment data over time using repeated measures MANOVA. Ancillary analyses to be run between the intervention and control arms include a proportion test for the patient’s readiness for hospital discharge. Additionally, an evaluation of feasibility, acceptability, and satisfaction will be summarized for inclusion when discussing the cost or benefit of the intervention.

Using intent-to-treat, participants providing data at baseline and first check-in will be included. Missing data (eg, due to attrition) will be accounted for using multiple imputations via the mice package in R (R Core Team) [38]. Sensitivity to missing data will be assessed by comparing multiple imputations to complete case analyses.

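### The stated 80% power appears to belong to the average arm difference over 3 time points, whereas the named primary test is the time-by-treatment interaction over 4 occasions, with about 30% to 40% power for a sustained effect of the planned size

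*Protocol article*

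**What the plan says.** **Sample Size section.** The calculation was done in G*Power, but the procedure chosen there is not named. It states that "the power analysis was run with 2 groups (the control arm and the intervention arm"), later split into eight clinic-by-arm subgroups, and that "The model included 3 time points for measurements". The targets are conventional: "The desired power was always set to 0.8, and the nominal type I error was set to .05". Effect sizes come from a control mean of 1.9, an SD of 1.4 and a single intervention mean between 2.2 and 2.65. The correlation among repeated measures was "varied for a range of values from 0.05 (representing nearly uncorrelated measurements) to 0.3 (representing moderately correlated measurements"). The smallest total, 64, is introduced with "Under optimal conditions, where the correlation among repeated measures is minimal at 0.05 with a medium effect size of 0.25". The chosen total of 192 is introduced with "Assuming we want to detect a Cohen f of 0.15 with any size correlation up to 0.3 among repeated measures and no attrition".

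**Analysis Plan section.** "The primary variable of interest is knowledge of postbirth warning signs, measured on 4 occasions". Table 1 shows these to be baseline, 1-2 weeks, 3 months and 6 months. The primary analysis is a repeated measures MANOVA "with a time and treatment interaction as the primary analysis controlling for baseline demographic variables". The same section also foresees arm comparisons at each time point. It predicts both higher knowledge in the intervention arm throughout and a larger rise between time points. No power is given for the interaction.

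**The concern.** The sample size and the primary analysis seem to address different hypotheses. One control mean set against one intervention mean, with no time pattern, defines a difference in level between arms. The interaction asks whether that difference changes over time. Since randomised arms should be equal at baseline, a sustained benefit reaches the interaction test only through the step from baseline to follow-up, and the test spreads that step over 3 degrees of freedom.

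At stake is whether the 80% applies to the test that will decide the trial. If it does not, a real and lasting benefit of the planned size could yield a non-significant primary result. Readers of the protocol would have no warning of this.

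**Working it through.** **Inputs.** From the Sample Size section: f = 0.15, SD 1.4, correlation ρ from 0.05 to 0.3, m = 3 time points, 2 arms, alpha 0.05, N = 192 (96 per arm), no attrition. From the Analysis Plan and Table 1: 4 occasions including baseline. With two equal arms d = 2f = 0.30 SD, so the planned difference is 0.30 × 1.4 = 0.42 points.

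**Step 1: reproduce 192.** For the between-arm effect averaged over m visits, the noncentrality is λ = f²·N·m / (1 + (m − 1)ρ), with 1 and N − 2 df.
- ρ = 0.3: 80% power is first reached at N = 188. Groups of 8, two arms and four clinics mean steps of 64, so 188 becomes 192. At 192, λ = 0.0225 × 192 × 3 / 1.6 = 8.10 and power is 80.8%.
- ρ = 0.05: λ = 12.96 / 1.10 = 11.78 and power is 92.7%.
- f = 0.25: the formula gives 50 at ρ = 0.05, rounded to the stated 64, and 70 at ρ = 0.3, rounded to 128.
- f = 0.10: it gives 422 at ρ = 0.3, rounded to 448. The stated 512 does not reproduce.

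**Step 2: is it the between-arm test?** The totals alone do not decide this. G*Power's within-between interaction formula (2 arms, 3 time points, ρ = 0.05) gives 138 for f = 0.15 and 52 for f = 0.25, which also round to 192 and 64. The text does discriminate:
- It calls low correlation the best case and treats 0.3 as the upper limit that 192 must cover. For the interaction the order is reversed: f = 0.15 needs 138 at ρ = 0.05 but only 102 at ρ = 0.3.
- It obtains f from one mean difference: (2.2 − 1.9) / 1.4 / 2 = 0.107 and (2.65 − 1.9) / 1.4 / 2 = 0.268, in line with the stated 0.10 and 0.25.

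**Step 3: power of the named primary test.** The interaction is Hotelling's T² on the three within-woman contrasts. Under compound symmetry λ = (n/2)·Σ(δₜ − mean δ)² / (1 − ρ), with n = 96 and 3 and 188 df; δₜ is the arm difference in SD units at occasion t.

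For δ = (0, 0.3, 0.3, 0.3) the mean is 0.225 and the sum of squares is 0.0675. So λ = 48 × 0.0675 / 0.95 = 3.41 at ρ = 0.05 and 48 × 0.0675 / 0.70 = 4.63 at ρ = 0.3. Power is 30.3% and 40.3%; simulation gave 30.1% and 40.0%.

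Other profiles, in points at baseline and the three follow-ups:

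| Profile | Sum of squares | Power, ρ = 0.05 | Power, ρ = 0.3 |
|---|---|---|---|
| 0, 0.14, 0.28, 0.42 | 0.0500 | 23% | 30% |
| 0, 0.42, 0.42, 0.42 | 0.0675 | 30% | 40% |
| 0, 0.21, 0.42, 0.63 | 0.1125 | 49% | 63% |
| 0, 0.14, 0.42, 0.70 | 0.1475 | 61% | 76% |

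For the constant profile, 80% power would need about 618 women (ρ = 0.05) to 458 (ρ = 0.3). At 192 women it would need a difference of about 0.76 to 0.65 points.

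**Step 4: the alternative test.** For the average of the three follow-ups adjusted for baseline knowledge, the variance in SD² units is (1 + 2ρ)/3 − ρ², which is 0.364 at ρ = 0.05 and 0.443 at ρ = 0.3. With λ = 48 × 0.09 / variance, λ is 11.86 and 9.74, and power is 92.9% and 87.4%.

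**The case against.** **The powered test is inferred.** The article does not name the G*Power procedure, and the between-arm formula recovers 64 and 192 but not 512. A reader might take it as established that a main effect was powered; the documents do not go that far. The role given to correlation and the single mean difference are nevertheless strong evidence, and neither fits an interaction.

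**f = 0.15 could be meant as an interaction effect.** Entered that way, power would be 92% to 99%. But with the profile 0, D, D, D, f = D × √0.1875 / 2, so D = 0.69 SD or 0.97 points. That is an intervention mean of 2.87, above the highest mean considered (2.65).

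**The authors expect a growing gap.** This stands in part. A larger rise over time is one of their two stated predictions, and the interaction addresses it. A reader might infer that the primary test will probably fail whatever happens. That is not supported: the steepest profile above gives 61% to 76%. It is still short of 80%.

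**The wording is loose.** The sentence could describe a model that merely contains the interaction. The natural reading makes the interaction the primary test.

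**Two further inferences should not be drawn.** An interaction restricted to the three follow-ups would have power equal to alpha (5%) under a constant benefit, but that analysis is not planned: four occasions are specified. The absence of a testing order for the time-point comparisons does not show an inflated type I error either. Such an order is commonly left to the SAP, which is not shown, and nothing says those comparisons would replace a failed primary test.

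**Conclusion.** The point holds in this form: the stated power is not a property of the stated primary test. At 192 women, the interaction over 4 occasions has about 30% to 40% power for a sustained 0.42-point benefit and about 23% to 76% across the profiles checked, against the 80% claimed. These figures assume no baseline difference, compound symmetry, correlations from 0.05 to 0.3 and no attrition. Adjustment for demographic variables is not modelled, because the article gives no figure for how much variance they explain.

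A reader might conclude that the trial is too small. The documents do not support that: 192 is adequate for the average arm difference at f = 0.15 under the plan's own assumptions. The fault lies in which test is called primary, or in which power is quoted for it.

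**What to change.** Before any follow-up data are compared by arm, amend the Analysis Plan so that the primary test is the 1-df arm difference in knowledge averaged over 1-2 weeks, 3 months and 6 months, adjusted for baseline knowledge. Keep the time-by-treatment interaction as a secondary analysis, so that the prediction of a larger rise is still examined.

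In the Sample Size section, name the test behind the calculation. State that the 80% at f = 0.15 refers to the unadjusted average at correlation 0.3 (about 81%; about 93% at 0.05), and that the baseline-adjusted test has about 87% to 93% under the same assumptions without attrition.

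If the interaction is to stay primary, which is a legitimate choice, replace the 80% with its actual power for the planned difference and state the assumed profile over time.

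The cost is small: no extra women or data. The drawback is that the primary analysis would change after enrolment is complete, in an unblinded trial with sessions underway. The amendment should therefore be dated and should document that no outcome comparison by arm has been seen.

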## Methods

### Study Design

This is a parallel randomized controlled trial with balanced randomization (1:1) conducted in 4 health centers in Sagnarigu municipality, Tamale, Ghana. An overview of the study design can be found in Textbox 1*.*

Study design.Recruitment of potential participantsEnrollment of eligible participantsInformed consent and baseline surveyRandom assignment into intervention and control groups:Kanvilli: 48 participants (intervention: n=24 [3 groups of 8]; control: n=24)Choggu: 48 participants (intervention: n=24 [3 groups of 8]; control: n=24)Kalpohin: 48 participants (intervention: n=24 [3 groups of 8]; control: n=24)Bagabaga: 48 participants (intervention: n=24 [3 groups of 8]; control: n=24)Focused Postpartum Care (Focused-PPC; intervention arm)Focused-PPC careFocus group discussions at endStandard postnatal care (control arm)Usual careNot applicableInterviewer administered surveys at certain time points (see Table 1) for both arms

**Table 1 table1:** Outcomes and evaluation.

Variables	Measurement	Baseline	1-2 weeks	6 weeks	3 months	6 months	12 months
Independent variables and potential covariates	Demographic questions, Obstetric history questions, Readiness for Hospital Discharge Scale – New Mother Form	✓					
Knowledge of postbirth warning signs	Investigator developed questions based on common postbirth complications	✓	✓		✓	✓	
Postpartum health behaviors	Specific questions assessing health behaviors will be tailored to the time frame post partum. Will include attendance to visits		✓	✓	✓	✓	✓
Postpartum health status	Edinburgh Postnatal Depression Scale, Perceived Stress Scale, Questions on complications experienced and other questions on health status as appropriate to the time frame after delivery, Measures of blood pressure, temperature, pulse, and weight	✓	✓	✓	✓	✓	✓
Feasibility, acceptability, and satisfaction	Focus groups with midwives and each group of participants in Focused-PPC^a^ intervention arm using focus group discussion guide						At exit

^a^Focused-PPC: Focused Postpartum Care.

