### Randomization

Project assistants will meet with eligible participants after birth, at discharge, in a designated private spot at the health facility, where they will obtain consent and complete the baseline survey. After the baseline survey, participant allocation will be 1:1 for equal intervention and control sizes. Allocation will be completed according to a computer-generated list of random numbers, allocating group sizes of 8. The allocation will be generated by a data scientist on the research team. The data scientist will provide participant allocations (intervention arm or control arm) to the project team. Participants in the intervention arm will also receive a group allocation (allocated in groups of 8). Intervention arm group participants will then be contacted to begin their group postpartum care. There will be no blinding, as the study team will know which women are in the intervention arm (receiving Focused-PPC) and the control arm (receiving usual care).

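### Arms are balanced 24:24 within each of the four health centres, but the stated primary model names no centre term, so standard errors for the arm differences are modestly too large if centres differ

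*Protocol article*

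**What the plan says.** Three parts of the protocol article's Methods treat centre as a feature of the design.

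- Study Design (Textbox 1) gives the same split for all four sites, for example "Kanvilli: 48 participants (intervention: n=24 [3 groups of 8]; control: n=24").
- Sample Size states that "Individuals at every health center will be randomly assigned to an intervention arm". It describes two arms "which were then split up into 8-equal sized subgroups (health center A intervention, health center A control" and so on through centre D.
- Randomization adds that "Allocation will be completed according to a computer-generated list of random numbers, allocating group sizes of 8". It does not use the word stratified, so balance by centre rests on Textbox 1 and Sample Size. The Results section confirms three intervention groups at each site.

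The Analysis Plan sets out a test of the arm difference in knowledge at each time point and a repeated measures MANOVA "with a time and treatment interaction as the primary analysis controlling for baseline demographic variables". Centre is not named there. The candidate covariates in Table 1 are demographic questions, obstetric history and readiness for discharge.

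**The concern.** With equal numbers per arm in every centre, a centre's mean level of knowledge adds equally to both arms and drops out of the arm difference. If the model has no centre term, that variation still sits in the residual. The reported standard error then describes a less precise trial than the one that was run.

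Centres could plausibly differ. Control women receive their own centre's usual care, each centre supplies its own midwives, and the project assistants who administer the surveys are employed centre by centre. Baseline demographics need not capture any of this.

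At stake is some precision in the arm comparisons at each visit and overall. The planned power has little margin to spare.

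**Working it through.** **1. The plan's own figure.** Inputs from Sample Size: Cohen f = 0.15, correlation up to 0.3, no attrition, power 0.80, alpha 0.05, and "The model included 3 time points for measurements". For a two-group between-subjects F test,

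λ = f²·N·m / (1 + (m−1)ρ) = 0.0225 × 192 × 3 / 1.6 = 8.1.

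With 1 and 190 degrees of freedom this gives power 0.808. The smallest N reaching 0.80 is 188. Whole groups of 8 in two arms and four centres need multiples of 64, so the total is 192, as stated. The detectable difference is 2 × 0.15 × 1.4 = 0.42 points.

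**2. Cost of a centre term if centres do not differ.** The error degrees of freedom fall from 190 to 187. Minimum N moves from 188 to 190, which still rounds to 192, and power stays at 0.808.

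**3. Standard error without centre.** Scale single-visit variance to 1, let s be the centre share (assumed), and let the total correlation be 0.3. The variance of a woman's mean over three visits is (1 + 2 × 0.3)/3 = 0.533.

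With four centres of 48, the expected between-centre sum of squares is 48 × 3 × s = 144s, spread over 190 residual degrees of freedom. So 144/190 = 0.758 of s enters the error. The ratio of the standard error without centre to that with centre is

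- single visit: √(1 + 0.758s/(1 − s))
- three-visit average: √(1 + 0.758s/(0.533 − s))

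| Assumed s | Single visit | Three-visit average | Type I error, average |
|---|---|---|---|
| 2% | 1.008 | 1.015 | 4.7% |
| 5% | 1.020 | 1.038 | 4.2% |
| 10% | 1.041 | 1.084 | 3.4% |

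The last column is 2 × (1 − Φ(1.96 × ratio)). Simulated ratios agree with the table, and simulated error rates lie within about 0.3 percentage points of it. Simulated power for 0.42 points, with the 0.3 correlation taken within centres, is about 0.81 without centre at all three shares. With centre it is about 0.82, 0.83 and 0.84.

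**4. The time-by-treatment term.** For a change between two visits, a centre effect that is constant over time cancels, and the simulated ratio is 1.000. If centres differ in change over time, the simulated ratio is 1.029 and 1.057 for assumed centre-by-time shares of 5% and 10%, with type I error about 4.5% and 4.0%.

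**5. Group clustering.** Let g be the share of variance between the 12 intervention groups of 8, and let v = 0.533 − s. The true variance of the three-visit arm difference is ((v + 7g) + v)/96. The model assumes about 2v/96 with centre and 2(v + 0.758s)/96 without.

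At assumed s = 5% and g = 5%, v = 0.483:

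- true numerator: 0.833 + 0.483 = 1.317
- model with centre: 0.967, so type I error = 2 × (1 − Φ(1.96 × √(0.967/1.317))) ≈ 9.3%
- model without centre: 1.042, so type I error ≈ 8.1%

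Across s = 2% to 10% at g = 5%, the range is about 7% to 9% without centre and about 9% to 10% with centre alone.

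**The case against.** **Silence is not exclusion.** This is a condensed article, and its adjustment clause lists no individual variables and does not say that they are the only ones. A full analysis plan could name centre. That is fair. Still, the article does describe the adjustment set for its primary analysis, and that set omits the factor on which the arms are balanced. The point is to state it.

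**Centres may hardly differ.** All four are Ghana Health Service centres in one municipality on one visit schedule, and nowhere is usual care said to differ between them. This stands: every size given here rests on an assumed centre share.

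**Stronger readings that the documents do not support:**

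- *The primary interaction test is conservative.* A constant centre effect cancels from it. Only centre differences in change over time matter, and nothing in the article shows any.
- *The trial's tests as a whole are conservative.* That would require no clustering within the intervention groups. A modest amount reverses the direction.
- *The loss is larger.* Putting the whole share s into the error gives √(0.533/(0.533 − s)) = 1.019, 1.050 and 1.109. That holds only if s is the realised spread among these four centres. Treated as a variance component, about three quarters of it enters.
- *The sample size fails.* Leaving group clustering aside, power without centre stays at about 0.81.
- *The secondary MANOVAs share the fault.* Those described are run in the intervention arm only, so they have no arm contrast to correct.

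**Conclusion.** The mismatch is real and modest. Arms are balanced by centre, and the stated model does not use centre. Considered alone, the omission makes standard errors for the arm differences in knowledge too large whenever centres differ in mean level. For assumed shares of 2% to 10%, the excess is about 1% to 4% at a single visit and 1.5% to 8% for the three-visit average. It costs precision and does not by itself raise the false-positive risk.

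The interaction that the plan makes primary is untouched unless centres differ in change over time.

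These sizes assume a correlation of 0.3, complete data and no group clustering. With such clustering the net direction is unknown, and a centre term alone would not put it right.

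**What to change.** In the Analysis Plan, state that the between-arm models for knowledge, and for any other outcome compared between arms, include health centre (four levels) and centre-by-visit as fixed effects. This uses 3 degrees of freedom per visit, needs no new data and leaves the sample size at 192. Enrolment is complete, so it should be fixed before the outcome data are analysed.

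Handle the 12 intervention groups in the same model, for example with a mixed model that has a group random effect in the intervention arm. This is a larger change than adding a covariate, because it replaces the MANOVA. The two changes should be made together: where groups are correlated, adding centre alone moves type I error further above 5%.

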The primary outcome is knowledge of postbirth warning signs, measured through questions developed based on an evidence-based assessment of the most common postbirth complications. The secondary outcome is postpartum health behaviors, including specific questions assessing health behaviors tailored to the specific time frame postpartum. Other descriptive outcomes include postpartum health status, which will include measures of postpartum depression, stress, complications experienced, vital signs, and other questions on health status as appropriate to the time frame after delivery. Postpartum depression is measured through the Edinburgh Postnatal Depression Scale (EPDS), a self-report screening tool commonly used in perinatal settings [34,35]. The EPDS consists of 10 items assessing women’s depressive symptoms over the past week. The EPDS has a maximum score of 30, with higher scores indicating higher frequency and increased severity of depressive symptoms. Stress is measured through the Perceived Stress Scale (PSS), a 10-item scale assessing women’s stress levels over the last month [36]. The PSS evaluates a woman’s perceptions of unpredictability, lack of control, and overloading in her life, with a higher score indicating higher levels of perceived stress. The feasibility and acceptability of the intervention will be measured using end-project focus group discussion data obtained from midwives and participants in the intervention arm. Outcomes and time points of data collection can be found in Table 1.

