## Discussion

### Principal Findings

The purpose of this study is to implement and evaluate a postpartum care model entitled Focused-PPC in a parallel randomized controlled trial with 192 postpartum women at 4 health centers in Tamale, Ghana. Focused-PPC sessions are underway in all participating health facilities. The primary outcome is knowledge of post-birth warning signs. We expect that the Focused-PPC group will have higher knowledge of post-birth warning signs than the control group at every time point measured and that the Focused-PPC group will have a larger increase in knowledge of postbirth warning signs between time points. We are also measuring postpartum health behaviors such as eating a healthy diet, uptake of family planning, breastfeeding, and so on. We expect that more participants in the Focused-PPC groups will eat a balanced diet most days of the week and uptake family planning compared to participants in the control groups. Additionally, we also expect mental health outcomes such as positive depression screens to be significantly lower over time in the Focused-PPC group compared to the control group. Other descriptive outcomes include postpartum health status, and we expect to capture and treat blood pressure cases during the course of the study.

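### The only analysis named for health behaviors and health status is change within the intervention arm, which cannot test the between-arm differences the protocol expects

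*Protocol article*

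**What the plan says.** **Status of the outcomes.** Data Collection or Measures ranks them: "The secondary outcome is postpartum health behaviors". Health status (EPDS, PSS, complications, vital signs) is listed there among other, descriptive outcomes.

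**What is expected.** The Analysis Plan opens with a general statement, "Differences in outcomes between the intervention and control arms will be assessed", and adds: "We expect postpartum health behaviors to be different between the intervention and control arms". Principal Findings is more specific. It predicts that more intervention women will "eat a balanced diet most days of the week and uptake family planning compared to participants in the control groups", and that the team will see "positive depression screens to be significantly lower over time in the Focused-PPC group compared to the control group".

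**What is to be done.** The Analysis Plan gives knowledge of warning signs a time-by-treatment model. Its next sentence covers the other outcomes: "For the intervention arm, follow-up secondary analyses will measure the change in postpartum health status, postpartum health behaviors, and clinical assessment data over time", by repeated measures MANOVA. The one further between-arm test it names is on readiness for hospital discharge.

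**What is collected.** The Study Design textbox says both arms are surveyed, and Data Collection or Measures says all participants are. Table 1 has health status at baseline and five follow-up visits. Health behaviors are at the five follow-up visits only, using "specific questions assessing health behaviors tailored to the specific time frame postpartum".

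**The concern.** The expectations compare arms, and the named method does not. Depressive symptoms, stress, vital signs, breastfeeding and family planning use can all be expected to move during the year after birth, whatever care is given. A significant time effect among intervention women would therefore be compatible with a real effect of Focused-PPC, with none, or with a harmful one. Randomization supplies the control arm that would tell these apart, but the named method does not use it.

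At stake is the trial's one secondary outcome, together with a depression result that the Discussion predicts in terms of significance against control. An analyst who followed the sentence as written would report uncontrolled before-after comparisons on these outcomes inside a randomized trial.

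**Working it through.** **1. Expectation against method**

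| Outcome | Status | Stated expectation | Named analysis |
|---|---|---|---|
| Knowledge of warning signs | Primary | Between arms | Between arms, time by treatment |
| Health behaviors | Secondary | Between arms | Within intervention arm |
| Health status, including EPDS | Descriptive | Between arms, for depression screens | Within intervention arm |
| Readiness for discharge | Covariate, baseline only (Table 1) | None | Between arms |

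The last row cannot fill the gap. The Randomization section places allocation after the baseline survey, so readiness is a pre-randomization variable and cannot show an intervention effect.

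**2. The protocol's own figure**

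The only sample size stated, 192, was derived for knowledge, and it reproduces. For the between-arms F test in repeated measures, lambda = f² × N × m / (1 + (m − 1) × rho). With f = 0.15, m = 3, rho = 0.3 and N = 192, lambda = 0.0225 × 192 × 3 / 1.6 = 8.1. On 1 and 190 degrees of freedom this gives power 0.808. The smallest N reaching 0.80 is 188, which rounds up to 192 as a multiple of 64 (4 centers × 2 arms × 8 women). At 1:1 allocation this leaves 96 women per arm.

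**3. What a one-arm test responds to**

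Suppose there is no intervention effect and both arms change by the same amount d, in SD units. A paired comparison of two visits in one arm has SD of change sqrt(2 × (1 − rho)) and noncentrality d × sqrt(n) / sqrt(2 × (1 − rho)).

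With n = 96, rho = 0.3 and d = 0.3, the SD of change is sqrt(1.4) = 1.183 and the noncentrality is 0.3 × 9.798 / 1.183 = 2.48. On 95 degrees of freedom, two-sided 5%, the chance of significance is 0.691. Over a range:

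| Shared change | rho 0.05 | rho 0.3 | rho 0.5 |
|---|---|---|---|
| 0.2 SD | 29% | 37% | 49% |
| 0.3 SD | 56% | 69% | 83% |
| 0.4 SD | 80% | 91% | 97% |

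A between-arm test of the intervention effect would reject 5% of the time in every cell. The values of d are assumptions. Rho from 0.05 to 0.3 is borrowed from the Sample Size section, where it refers to knowledge; 0.5 is an assumption. The paired test simplifies the MANOVA.

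**4. What a between-arm comparison could detect**

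At one visit with 96 per arm, the difference detectable with 80% power is (1.960 + 0.842) × sqrt(2/96) = 0.404 SD. For yes/no outcomes at assumed rates, power is 81% for 30% against 50%, 70% for 30% against 15%, and 49% for 20% against 10%. These figures allow for neither attrition nor clustering within groups.

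**5. Fit of the MANOVA**

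A repeated measures model needs the same quantity at each visit. Behavior items that vary by visit and lack a baseline do not supply one. EPDS, PSS, blood pressure, temperature, pulse and weight do, since Table 1 lists them at all six time points.

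**The case against.** The strongest reply is that a between-arm comparison is already declared. The opening sentence, "Differences in outcomes between the intervention and control arms will be assessed", speaks of outcomes in the plural and is not confined to knowledge, so all that is missing is a model, which a condensed article may leave to an analysis plan. On this reading the intervention-arm sentence is an additional analysis. It also covers clinical assessment data, part of which comes from group sessions that only one arm attends. The list of ancillary between-arm analyses is worded as non-exhaustive, and health status is declared descriptive.

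Much of this stands. The opening sentence shows intent, and a one-arm summary of a descriptive outcome is not wrong in itself. It does not settle the matter, because the article does more than leave a model open. When it reaches the secondary outcome it names an analysis and confines it to one arm, against its own expectation two paragraph-lengths at most away. The general sentence conflicts with that restriction and offers no test to replace it. For depression screens, the descriptive label sits beside a prediction of significance against control.

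Four stronger readings are tempting and are not supported:

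- That the trial itself cannot show these differences. It can: both arms are randomized and surveyed.
- That control data will go unused, or that natural recovery will be reported as benefit. The document says neither.
- That 69% is a false-positive rate. Rejecting no change when a change exists is a correct rejection. The figure shows only that the one-arm test answers a different question from the between-arm test.
- That MANOVA suits none of these outcomes. The misfit is limited to the visit-tailored behavior items.

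**Conclusion.** The point holds as a contradiction between the stated expectations and the only analysis named for them. It covers the single secondary outcome in full. It covers health status to the extent that the Discussion predicts a between-arm result on depression screens. The conclusion rests on the text and needs no numerical assumption.

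The 69% figure illustrates the consequence under an assumed shared change of 0.3 SD, correlation 0.3 and a paired test in place of the MANOVA; for a 0.3 SD change it runs from 56% to 83% across the correlations tried. The fault lies in the analysis wording and leaves the design, the sample size and the primary analysis of knowledge untouched.

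**What to change.** Replace the intervention-arm-only sentence in the Analysis Plan with between-arm analyses:

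- **Health behaviors:** compare arms at each visit where an item is asked. For yes/no items such as family planning uptake, use a binary-outcome model that gives a risk difference or risk ratio with its confidence interval.
- **Positive EPDS screen:** the same kind of between-arm binary comparison at each visit.
- **EPDS score, PSS and vital signs:** a repeated measures model with arm, visit and arm-by-visit terms, adjusted for the baseline value where one was collected.
- **Within-arm change:** keep it, labelled descriptive, including for session clinical data that exist in the intervention arm alone.

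The cost is revised wording and a few extra models on data already planned in both arms. No new participants, visits or questions are needed.
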